### Randomization and allocation

2.7

Given the importance of randomization on the one hand and the need for balanced sample sizes between the studied groups on the other hand, the random permutation block method is used. For this purpose, random permutation blocks of length 4 with two interventions are generated, and patients are allocated to the intervention arms accordingly. Allocation will be concealed in sealed envelopes prepared by an independent researcher.

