### Study setting

2.2

The clinical trial will be conducted at the ICU of Hazrat Rasool Akram Hospital in Tehran under the joint academic supervision of Mashhad University of Medical Sciences and Iran University of Medical Sciences. Both institutions collaborate in the oversight of study implementation, adherence to ethical standards, and data quality assurance. The study subjects will be critically ill patients admitted to the ICU 24 h after admission. The participants will be selected via a simple random sampling method. Eligible patients will be between 18 and 65 years old and categorized under general ICU admission.

A total of 88 critically ill patients who fulfill all the inclusion and exclusion criteria will be recruited on the basis of previous studies and sample size calculations. The principal investigator ([name]) After providing informed consent from the patient's legal guardian—following a full explanation of the study's objectives and procedures, emphasizing confidentiality and voluntary participation—patients will be randomly allocated to either the control or intervention group, with 44 patients in each. Recruitment procedures will involve in-person visits to the ICU by the research team. Throughout the study period, all participants will be monitored under the supervision of a board-certified intensive care specialist ([name]).

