### Blinding

2.8

Patients will be assigned to either an HP diet or a CP intake plan. We acknowledge that complete blinding in nutritional intervention trials may be challenging, particularly when individualized protein targets or supplemental parenteral nutrition are required. The nutritional formulations provided in both groups will be visually indistinguishable, share similar color, texture, and packaging, and will be delivered in identical containers labeled with unique codes. Protein dosing will be adjusted by an ICU-based clinical dietician unaffiliated with the research team to ensure healthcare personnel remain blinded. As a result, healthcare personnel, including medical and nursing staff, will be blinded to the nutritional content administered to each participant. Given patients’ critical illness and reduced consciousness, they are not aware of their treatment assignment, which inherently reduces the risk of patient-level bias. If supplemental parenteral nutrition is required, it will be documented and considered in the analysis to minimize bias. Outcome assessments, including serum zonulin measurements, clinical scoring systems such as SOFA scores, and mortality rates, will be assessed by blinded independent raters without knowledge of the groups to which the patients were allocated. APACHE II and mNUTRIC scores were assessed only at ICU admission. All the data will be coded and deidentified prior to statistical processing, and the biostatistician will remain blinded until the final analysis is completed.

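### The single published block length of 4 leaves concealment resting on masking that the protocol says may be incomplete; randomly varied, undisclosed block lengths are a cheap improvement

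*Protocol article*

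**What the plan says.** Section 2.7 (Randomization and allocation) sets the method: "random permutation blocks of length 4 with two interventions are generated". It gives one length and mentions no variation. On concealment it says: "Allocation will be concealed in sealed envelopes prepared by an independent researcher".

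Section 2.2 (Study setting) places the whole trial in one unit ("The clinical trial will be conducted at the ICU of Hazrat Rasool Akram Hospital in Tehran") with equal arms ("patients will be randomly allocated to either the control or intervention group, with 44 patients in each"). It also says who enrols patients and where: "Recruitment procedures will involve in-person visits to the ICU by the research team".

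Section 2.8 (Blinding) opens with a caution: "We acknowledge that complete blinding in nutritional intervention trials may be challenging". It then lists safeguards. The feeds look alike and "will be delivered in identical containers labeled with unique codes"; medical and nursing staff are blinded to content; outcome raters and the biostatistician are blinded; and "Protein dosing will be adjusted by an ICU-based clinical dietician unaffiliated with the research team". It does not state that the recruiting research team is blinded to the allocations of patients already entered.

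The Trial registration section says that recruitment had not yet begun.

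**The concern.** Envelopes hide the next assignment physically. They do not stop someone from deducing it who knows the block length and the earlier assignments in the block. With one known length of 4, a person who counts enrolments knows where each block starts, and once two patients in a block are known to share an arm, the rest of that block is determined.

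Masking is therefore what stands between the published block length and prediction of the next arm. The protocol qualifies that masking in its own words and leaves the recruiters out of the list of blinded people. Recruitment takes place in the same unit where earlier patients are being fed.

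The possible harm is selective enrolment: whether or when an eligible patient is entered could depend on the arm expected next. The covariates in section 2.10.16 adjust for measured differences between arms, but not for unmeasured differences that arise in this way.

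**Working it through.** **Inputs.** Block length 4, two arms (2.7). Equal allocation, 44 + 44 = 88 (2.2), so 88/4 = 22 complete blocks. The share q of earlier allocations that a recruiter knows is not given in the article; it is an assumption and is varied from 0 to 1. The protocol states no predictability figure, so there is none to reproduce.

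**Certain allocations, everything earlier known (q = 1).** A block of two A and two B has six equally likely orders.
- AABB and BBAA: the first two patients exhaust one arm, so the third and fourth are fixed (2 positions each).
- ABAB, ABBA, BABA, BAAB: only the fourth is fixed (1 position each).
- Mean fixed per block = (2×2 + 4×1)/6 = 1.333 of 4 = 33.3%. Over 88 patients this is 88/3 = 29.3.

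This is an average. One block fixes 25% or 50% of its patients. Across 22 blocks the number fixed is 22 + X, with X ~ Binomial(22, 1/3). The central 95% range is 25 to 34 patients (28% to 39%), and 46% of lists exceed one third.

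**Best guess, everything earlier known.** Always guess the arm with more places left in the block. The chance of being right is 1/2 at position 1, 2/3 at position 2, (1/3)×1 + (2/3)×(1/2) = 2/3 at position 3, and 1 at position 4. The sum is 2.833, and 2.833/4 = 70.8%, against 50% by chance.

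**Partial knowledge.** Suppose each earlier allocation is known independently with probability q.
- Position 3 is certain if positions 1 and 2 share an arm (probability 1/3) and both are known: q²/3.
- Position 4 is certain if the two patients in the arm already filled are both known: q².
- Certain share = (q²/3 + q²)/4 = q²/3.

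| q | Certain share | Patients of 88 |
|---|---|---|
| 0 | 0% | 0 |
| 0.25 | 2.1% | 1.8 |
| 0.5 | 8.3% | 7.3 |
| 0.75 | 18.8% | 16.5 |
| 0.9 | 27.0% | 23.8 |
| 1 | 33.3% | 29.3 |

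**Effect of varying the length.** Lists of 88 were simulated with block lengths drawn at random. The guesser knows all past allocations and which lengths are in use, but not the length of each block.

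| Block lengths | Certain share | Best guess right |
|---|---|---|
| 4 only | 33.3% | 70.8% |
| 4 and 6 | 5.7% | 69.1% |
| 4, 6 and 8 | 2.4% | 67.9% |

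Varying the length removes most of the certainty but little of the guessing advantage. Guessing the arm that is behind remains a good strategy whenever past allocations are known.

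**The case against.** The strongest reply is that block length alone makes nothing predictable. The trial is described as double-blind, the envelopes are independently prepared, the feeds are look-alike and coded, and clinical staff are blinded. The remark about incomplete blinding is a general caution, tied mainly to individualised targets and supplemental parenteral nutrition, and the safeguards follow it directly. Nothing in the article shows that recruiters learn allocations. This stands, and it is why the size must be stated conditionally.

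A reader might see the dietician as the leak, being based in the ICU and adjusting protein doses. The article does not support that: the dietician is placed outside the research team precisely to keep staff blinded, and no route from dietician to recruiter is described. What remains is only that the recruiters' own blinding is not stated.

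A reader might also infer that unstable patients could be steered into one arm, or that nothing later could help. Section 2.4 requires haemodynamic stability at inclusion; zonulin is measured before the intervention; and section 2.10.16 adjusts for age, sex, BMI, APACHE II and other factors. These limit the harm from measured imbalance, though not from unmeasured selection.

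Finally, varied blocks barely lower the best-guess rate. That is correct. It means that block length is not the whole remedy and that keeping recruiters unaware of earlier allocations matters more.

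**Conclusion.** The point holds as a modest weakness in a stated design choice. It is not an error or a contradiction. The protocol fixes one short block length, publishes it before recruitment in a single ICU, concedes that blinding may be incomplete, and does not state that recruiters are blinded.

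The size runs from no certain allocations if masking holds, through about 8% (7 patients) if half of the earlier allocations are known, to an average of one third (about 29 of 88) under full knowledge. It rests on three assumptions: q, which the article does not give; independence of what is known from patient to patient; and a recruiter who can count enrolments and so locate block boundaries.

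A reader might infer that up to one third of allocations are predictable as the plan stands. That is wrong in two ways. It needs every earlier allocation in the block to be known, which the article does not suggest, and one third is then the average and not a ceiling. Importance is minor to moderate.

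**What to change.** Before the first patient is entered:

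1. In 2.7, replace the fixed length with randomly varied block lengths, generated by the independent researcher who already prepares the envelopes.
2. Do not print the lengths in 2.7. Keep them in a restricted document that recruiters and ICU staff cannot see until recruitment ends. A mix of 4 and 6 is one example of what would serve; the lengths actually used should be chosen privately.
3. In 2.8, state that those who recruit are kept unaware of the allocations of earlier patients. Varied blocks cannot replace this, because they leave the best-guess rate near 69% if past allocations are known.

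The cost is one regenerated list, with no new role needed. The arms may end unequal by at most 3 patients if lengths go up to 6 and the list stops part-way through a block, where 22 complete blocks of 4 would end exactly equal. The ethics and registry records may need a minor amendment if they specify the block length. The change cannot be made later for patients already entered.

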### Blinding

2.8

Patients will be assigned to either an HP diet or a CP intake plan. We acknowledge that complete blinding in nutritional intervention trials may be challenging, particularly when individualized protein targets or supplemental parenteral nutrition are required. The nutritional formulations provided in both groups will be visually indistinguishable, share similar color, texture, and packaging, and will be delivered in identical containers labeled with unique codes. Protein dosing will be adjusted by an ICU-based clinical dietician unaffiliated with the research team to ensure healthcare personnel remain blinded. As a result, healthcare personnel, including medical and nursing staff, will be blinded to the nutritional content administered to each participant. Given patients’ critical illness and reduced consciousness, they are not aware of their treatment assignment, which inherently reduces the risk of patient-level bias. If supplemental parenteral nutrition is required, it will be documented and considered in the analysis to minimize bias. Outcome assessments, including serum zonulin measurements, clinical scoring systems such as SOFA scores, and mortality rates, will be assessed by blinded independent raters without knowledge of the groups to which the patients were allocated. APACHE II and mNUTRIC scores were assessed only at ICU admission. All the data will be coded and deidentified prior to statistical processing, and the biostatistician will remain blinded until the final analysis is completed.

### Sample size

2.9

The sample size was determined on the basis of serum zonulin levels, which were considered the primary outcome of the study. In the study by Klaus et al. [21], the mean zonulin level in the target patient population was reported to be 3.40 ng/mL, with a standard deviation of 0.71. A type I error (α) of 0.05 and a statistical power (1−β) of 80% were used for the calculation. A 10% change in zonulin levels was deemed clinically significant. This threshold was chosen based on previous reports of variation in zonulin levels in critical illness and feasibility considerations for sample size estimation [21]. The exploratory nature of this outcome is acknowledged. Using the standard formula for sample size estimation based on a two-sided independent samples *t*-test to determine the mean of the intervention group versus the control group, the required sample size was calculated to be 41 participants per group, or a total of 82 participants. The final sample size was adjusted to 44 participants in each group, out of a total of 88 participants, considering an expected attrition rate of 5% during the study period.

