**Methods:**

Participants were selected from 88 adult patients with critical illness aged 18-65 years who were admitted to the ICU of Hazrat Rasoul Akram Hospital in Tehran. In this randomized controlled clinical trial, patients will be allocated randomly into two groups of 44. The intervention group will receive high-protein (HP) enteral nutrition (1.6 g/kg/day), and the control group will receive conventional-protein (CP) enteral nutrition (1.2 g/kg/day) for 10 days. The primary outcome will be the change in serum Zonulin levels during the intervention period. Zonulin will be measured on days 0, 5, and 10. The SOFA, APACHE II, and mNUTRIC scores will also be assessed. Mortality will be calculated at 30 and 60 days after the intervention. The secondary outcomes will be SOFA score and 30- and 60-day mortality.

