#### Primary outcomes

2.10.4

•Zonulin levels will be measured to assess intestinal permeability.

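### The primary zonulin outcome is named as a change in one place and as a level elsewhere, and the 80% power, built on the SD of a single level, is unsupported for the change

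*Protocol article*

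**What the plan says.** The protocol article describes the primary outcome in four places.

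- **Abstract, Methods:** "The primary outcome will be the change in serum Zonulin levels during the intervention period". Sampling is on days 0, 5 and 10.
- **Section 2.9, Sample size:** "The sample size was determined on the basis of serum zonulin levels, which were considered the primary outcome of the study".
- **Section 2.10.4, Primary outcomes:** "Zonulin levels will be measured to assess intestinal permeability". No change score and no day is named.
- **Section 2.10.16, Statistical analysis:** the primary outcome is again given as zonulin levels. ANCOVA is planned for baseline, day 5 and day 10, alongside longitudinal regression and pre/post paired t-tests. The listed covariates are age, sex, BMI, APACHE II, admission diagnosis, vasopressor use and comorbidity groups. Day-0 zonulin is not among them.

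The inputs in Section 2.9 are a level and its spread, "the mean zonulin level in the target patient population was reported to be 3.40 ng/mL, with a standard deviation of 0.71"; an effect, "A 10% change in zonulin levels was deemed clinically significant"; the error rates, "A type I error (α) of 0.05 and a statistical power (1−β) of 80% were used for the calculation"; and a two-sided independent-samples t-test used "to determine the mean of the intervention group versus the control group". The result is 41 per group, raised to 44 for 5% attrition. The article states neither an SD of change nor a correlation between repeated zonulin values.

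**The concern.** A power statement applies only to the variable whose SD went into it. The SD of 0.71 describes the spread between patients of one zonulin level. The SD of a within-patient change also depends on how strongly the day-0 and follow-up values correlate, and may be larger or smaller than 0.71. If change is primary, as the abstract says, the article gives no basis for 80% power on it.

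The wording also leaves open a change score, a day-5 level or a day-10 level as the primary variable. These can have different power, and with three sampling days the choice should be fixed before data are seen. Correcting the arithmetic in Section 2.9 alone would not settle which variable the power refers to.

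**Working it through.** **Inputs from Section 2.9.** Mean 3.40 ng/mL, SD 0.71, difference 10% × 3.40 = 0.34 ng/mL, two-sided alpha 0.05, power 80%, equal arms.

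**Step 1: the plan's own figure.** For two means, n per arm = 2 × [(1.96 + 0.8416) × SD / difference]² = 2 × (2.8016 × 0.71 / 0.34)² = 68.5, so 69. The noncentral t calculation gives 69.4, so 70. The stated 41 is not reproduced. One-sided (54; 55 by t) and one-sample or paired (35; 37 by t) variants do not give it either. At 41 per arm the power for a level is about 57% (noncentral t). The attrition step is right: 41 / 0.95 = 43.2, so 44.

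**Step 2: SDs for the candidate variables.** The article gives no rho, so rho is an assumption shown over a range, with equal variance at both times.

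- Raw change: SD = 0.71 × √(2(1 − rho)). This equals 0.71 at rho = 0.5, is larger below and smaller above.
- Follow-up level adjusted for day 0: SD = 0.71 × √(1 − rho²). This never exceeds 0.71.

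Under randomisation the expected between-arm difference is the same for the change and for the follow-up level, so 0.34 serves both.

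**Step 3: power by noncentral t.**

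| rho | SD of change | Change, 41 per arm | Change, 70 per arm | n per arm for 80% (change) | SD adjusted | Adjusted level, 41 per arm |
|---|---|---|---|---|---|---|
| 0.3 | 0.840 | 44% | 66% | 97 | 0.677 | 61% |
| 0.5 | 0.710 | 57% | 80% | 70 | 0.615 | 70% |
| 0.7 | 0.550 | 79% | 95% | 43 | 0.507 | 85% |

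With 41 per arm, 80% is reached on raw change only at rho of about 0.71, and on the adjusted level only at rho of about 0.65.

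**Step 4: separating the two problems.** At rho = 0.5 the change SD equals the level SD, so the fall from 80% to 57% at 41 per arm is entirely the arithmetic error. The part due to the choice of variable shows in the 70-per-arm column: 66% at rho 0.3 and 95% at rho 0.7, against 80% for the level.

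**The case against.** The strongest reply is that the calculation fits the outcome as its own section names it. Only the abstract says change; Sections 2.9, 2.10.4 and 2.10.16 say levels. Section 2.10.16 plans ANCOVA and longitudinal regression, and nowhere an unadjusted between-arm test of raw change. If the ANCOVA adjusts for day-0 zonulin, the level SD is conservative at any rho. The 10% is applied in a test between the arms, so its role can be worked out from the context.

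Much of this stands. A reader might infer that the power claim must remain wrong even after 41 is corrected. The documents do not support that: with 70 per arm, power on raw change is below 80% only if rho is below 0.5, and a day-0-adjusted analysis has at least 80% at every rho of 0 or more. Nor do the low powers at 41 per arm measure this problem alone, since they carry the arithmetic error.

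Two things remain. The abstract contradicts the other three sections on what is primary, and nothing supplied supports 80% for a change. The defence through ANCOVA also assumes an adjustment for day-0 zonulin that the covariate list in Section 2.10.16 does not contain.

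**Conclusion.** The point holds as an inconsistency in the primary outcome together with an unsupported power claim for one of its two versions. It does not show that the level-based calculation chose the wrong SD for the outcome named in Section 2.9. Nor does it show that a correctly computed level-based sample size would be too small.

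The size depends on a correlation that the article does not give. For raw change with 70 per arm, power runs from about 66% (rho 0.3) to 95% (rho 0.7), crossing 80% at about 0.5. These figures assume equal variance at the two times, a true difference of 0.34 ng/mL and complete data. The larger and demonstrable defect in Section 2.9 is the arithmetic, 41 stated against 70 from the same inputs. The present point should be corrected alongside it, because repairing that number leaves the primary variable undecided.

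**What to change.** - Make the abstract and Sections 2.9, 2.10.4 and 2.10.16 name one primary variable at one time point: the zonulin level on a single stated follow-up day, adjusted for the day-0 level.
- Add day-0 zonulin to the ANCOVA covariates in Section 2.10.16. The value is already collected, and under the assumptions above the adjusted analysis is never less precise than the raw change or the unadjusted level.
- State in Section 2.9 that 10% (0.34 ng/mL) is the between-arm difference on that day.
- Restate the power in Section 2.9 for 41 analysed per arm with SD 0.71 × √(1 − rho²) over a declared rho range: about 61% at 0.3, 70% at 0.5 and 85% at 0.7, reaching 80% only at about 0.65.

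The cost is rewording, and the article says that recruitment has not begun. No extra patients are needed. The downside is a stated power that is below 80% over most of that range.

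### The stated 41 per group does not follow from the stated inputs, which require 70 per group; the named t-test has about 57% power, not 80%

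*Protocol article*

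**What the plan says.** Section 2.9 (Sample size) gives a complete set of inputs.

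- Reference values from a cited study: "the mean zonulin level in the target patient population was reported to be 3.40 ng/mL, with a standard deviation of 0.71".
- Target difference: "A 10% change in zonulin levels was deemed clinically significant".
- Error rates: "A type I error (α) of 0.05", and power "of 80% were used for the calculation".
- Method: "Using the standard formula for sample size estimation based on a two-sided independent samples" *t*-test, intervention against control.
- Result: "the required sample size was calculated to be 41 participants per group, or a total of 82 participants".
- After a 5% allowance for attrition: "The final sample size was adjusted to 44 participants in each group, out of a total of 88 participants".

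The section gives no baseline-to-follow-up correlation, SD of change or one-sided test. The Statistical analysis section (2.10.16) plans ANCOVA and longitudinal regression with covariates for zonulin, but the sample size section does not use them.

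**The concern.** Everything needed to recompute the sample size is in one paragraph, and the result is well below what those inputs give. Zonulin is the only primary outcome, and this is the only power statement in the article. If 41 per group is too few, the chance of missing a true 10% difference is about twice the 20% the protocol accepts. A non-significant result would then be easy to misread as evidence against a 10% effect, in a trial whose Discussion hopes to inform guidelines on protein dosing.

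**Working it through.** **Inputs (all from section 2.9).** Mean 3.40 ng/mL; SD σ = 0.71; relevant change 10%; two-sided α = 0.05; power 80%; two independent groups, 1:1.

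**Difference.** δ = 0.10 × 3.40 = 0.34 ng/mL. Standardised difference d = 0.34 / 0.71 = 0.479.

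**Sample size, normal approximation.** n per group = 2 (z₀.₉₇₅ + z₀.₈₀)² (σ/δ)² = 2 × (1.960 + 0.8416)² × (0.71/0.34)² = 68.5, rounded up to 69.

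**Sample size, t-test (noncentral t).** n = 69.4, rounded up to 70. Power is 79.8% at 69 and 80.3% at 70. The total is 140 evaluable patients. With the protocol's 5% attrition, 70/0.95 = 73.7, so 74 per group and 148 in total.

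**Attempts to reproduce 41.**

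| Variant | n per group |
|---|---|
| As stated (two-sided, two-sample) | 69 (normal), 70 (t) |
| Rounding of mean and SD (3.395 to 3.405; 0.705 to 0.715) | 68 to 70 (normal) |
| One-sided 5% | 54 (normal), 55 (t) |
| One-sample or paired formula | 35 (normal), 37 (t) |
| SD proportional to the mean | 62 |
| Log scale | 62 to 76 |

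None gives 41. Values at or near 41 appear only with inputs that the text contradicts or does not state: one-sided α of 0.10 (40), one-sided 5% with 70% power (42), a difference of 13% (41), an SD of about 0.54 to 0.55 (41), ANCOVA with an assumed correlation of about 0.64 (41), or a change score with an assumed correlation of about 0.70 (42).

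**Attrition step.** 41/0.95 = 43.2, rounded up to 44. This reproduces, so the fault lies in the step before it.

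**Power of the stated t-test at δ = 0.34 ng/mL.**

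| Evaluable per group | Power |
|---|---|
| 41 | 57.2% |
| 44 | 60.3% |
| 70 | 80.3% |

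**Difference detectable with 80% power at 41 per group.** d = 0.626, so 0.626 × 0.71 = 0.445 ng/mL, which is 0.445/3.40 = 13.1%. Relative to the stated difference, 0.445/0.34 = 1.31.

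**If a day-10 ANCOVA adjusted for day 0 is used instead.** The residual SD is 0.71 × √(1 − ρ²), where ρ is the day-0 to day-10 correlation. The documents do not give ρ, so the values below are assumptions.

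| Assumed ρ | Power at 41 per group, 0.34 ng/mL |
|---|---|
| 0.50 | 69.6% |
| 0.65 | 80.5% |
| 0.70 | 85.1% |

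**The case against.** The strongest reply is that 57% is the power of an unadjusted comparison at one time point, which is not the planned primary analysis. Section 2.10.16 plans ANCOVA and longitudinal models on days 0, 5 and 10, and these could do better. Suppose all three visits are equally correlated (ρ), the effect is a constant 0.34 ng/mL, and the mean of days 5 and 10 is adjusted for day 0. The variance factor is then (1 + ρ)/2 − ρ², at most 0.5625 (at ρ = 0.25), and power at 41 per group is at least 81% for any non-negative ρ. A different assumed structure (0.7 between days 5 and 10, 0.3 between days 0 and 5, 0.2 between days 0 and 10) gives about 68%.

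This part stands: the power of the eventual analysis is unknown, it could exceed 80%, and the 57% should be attached to the test that section 2.9 names. It does not rescue the figure 41, because section 2.9 bases that number on the t-test and no correlation is stated anywhere.

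It is also fair to say that the text does not show which figure is wrong. The mean and SD come from a source not at hand, and a slip in the SD or the percentage would explain 41 as well as a slip in the calculation. That is a reason to recheck the inputs first.

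Finally, section 2.9 calls the outcome exploratory and mentions feasibility in choosing the 10% threshold. Neither remark alters the arithmetic, since the text still presents 41 as the number required for 80% power. The article states no rule for interpreting a null result, so the risk of misreading one is a judgement.

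**Conclusion.** The concern holds. On the protocol's own inputs the named test needs 70 per group (69 by the normal approximation), 29 more than stated. For 0.34 ng/mL the risk of missing a true difference is about 43% with 41 evaluable per group and 40% with 44, against the 20% claimed. These figures assume that the mean of 3.40 and SD of 0.71 are transcribed correctly, that the 10% is taken of that mean, and that the unadjusted two-sided t-test is the basis, as written. An adjusted or longitudinal analysis may have more power, but only under correlation assumptions that the article does not make. The sample size and power statement is wrong as written and must be corrected.

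**What to change.** First recheck the mean, SD and percentage difference against their source, and correct any transcription error. If the inputs stand, take one of two routes, both keeping 88 patients.

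1. Restate what the design delivers, for example: *With 41 evaluable patients per group, an SD of 0.71 ng/mL and a two-sided 5% t-test, power is 57% for a difference of 0.34 ng/mL (10%) and 80% for a difference of 0.445 ng/mL (13%).*
2. Base the calculation on the planned adjusted analysis, naming the time point or longitudinal contrast and the assumed correlations with their justification. For a day-10 ANCOVA adjusted for day 0, 41 per group reaches 80% power for 0.34 ng/mL at a correlation of about 0.65 or higher. Show the power over a range of values, such as 70% at 0.50 and 85% at 0.70.

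The cost is protocol wording only. The article reports that recruitment had not begun, so the correction can be made before any patient is enrolled. Under the first route, the price is a less favourable power or detectable difference.

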### Reasons for eliminating the data

2.6

•Expected ICU stay of less than 48 h•Patient death or discharge before day 4 of the study•Use of glutamine supplement during the study period•NPO (nil per os) status for more than 4 consecutive days•Presence of any absolute contraindication to EN•Refusal or withdrawal of consent at any stage of the intervention

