#### Secondary outcomes

2.10.5

•SOFA questionnaire•30-day and 60-day mortality rates•Length of stay (LOS) in a hospital

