#### Enteral protein administration

2.10.8

Gavages will be administered by personnel blinded to the baseline assessments. Once each patient's hemodynamic status is stabilized, tube feeding (via a nasogastric tube or gastrostomy) is initiated. High-protein feeding begins 48 h after ICU admission and continues until either ICU discharge or day 10 of the study. Enteral feeding will be given intermittently every 3 h. The feeding volume will be determined on the basis of each patient's caloric requirements and tolerance. During the first 24 h, 30% of the total caloric need will be initiated. If well tolerated, the volume was gradually increased to the target level. The protein and energy goals should be increased gradually and achieved within the first 48 to 72 h to avoid overfeeding.

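### The 5% attrition allowance in section 2.9 leaves room for only 3 losses per arm, has no stated source, and is not reconciled with the plan's own data-removal rules

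*Protocol article*

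**What the plan says.** Section 2.9 (Sample size) takes serum zonulin as the primary outcome and arrives at 41 per group, 82 in total. It then raises this to 44 per group, 88 in total, "considering an expected attrition rate of 5% during the study period". No source or breakdown is given for the 5%.

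Three other parts of the article bear on how many patients will have usable zonulin:

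- **Section 2.6** lists reasons for eliminating data. One is "Patient death or discharge before day 4 of the study". Others are glutamine use during the study, NPO status for more than 4 consecutive days, and withdrawal of consent at any stage.
- **Section 2.10.8** says that high-protein feeding "continues until either ICU discharge or day 10 of the study".
- **The Abstract (Methods)** defines the primary outcome as the change in zonulin over the intervention period and states: "Zonulin will be measured on days 0, 5, and 10".

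The secondary outcomes in section 2.10.5 include "30-day and 60-day mortality rates". The article describes no replacement of patients whose data are removed.

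**The concern.** The 80% power claim belongs to 41 patients per group with usable zonulin, not to 44 randomised. Going from one to the other, the plan allows a single 5% for everything that can go wrong in 10 days of intensive care. Its own list of removal reasons is long, and at least one reason, death or discharge before day 4, acts before the first post-baseline sample is due on day 5. Patients removed on that ground contribute no follow-up zonulin under any analysis model. Patients who die between day 5 and day 10 have no day-10 value.

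If the real loss is larger than the allowance, fewer than 41 per group will be evaluable. A null zonulin result could then be read as coming from a trial with 80% power when its power was lower.

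**Working it through.** **Inputs.** From section 2.9: "A type I error (α) of 0.05"; a calculation "based on a two-sided independent samples" t-test; power "of 80% were used for the calculation"; mean zonulin 3.40 ng/mL, SD 0.71; relevant change 10%, which is 0.10 × 3.40 = 0.34 ng/mL; 41 per group needed, 44 randomised, 5% attrition. The documents give no rate for death, discharge, NPO status or withdrawal. The loss rates below are therefore assumptions, shown as a range.

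**1. The inflation step.** 41 / (1 − 0.05) = 43.2, rounded up to 44. This reproduces the plan's figure. The margin is 44 − 41 = 3 per arm, or 3/44 = 6.8%. A fourth loss in an arm leaves 40.

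**2. How safe the margin is.** Let each patient be lost independently with probability q. The chance that one arm keeps at least 41 is P(Binomial(44, q) ≤ 3). For both arms, square it.

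| True loss q | Expected evaluable per arm, 44(1 − q) | One arm keeps ≥ 41 | Both arms keep ≥ 41 |
|---|---|---|---|
| 5% | 41.8 | 82% | 68% |
| 10% | 39.6 | 35% | 12% |
| 15% | 37.4 | 9% | 0.8% |
| 20% | 35.2 | 1.5% | 0.02% |

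Even when the 5% is exactly right, there is about a one in three chance that at least one arm ends below 41.

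**3. The base figure.** On the stated inputs the standardised difference is 0.34/0.71 = 0.479. The normal-approximation formula gives n = 2 × [(1.960 + 0.842) × 0.71/0.34]² = 68.5, so 69 per group. The exact t-test gives 69.4, so 70. The stated 41 does not reproduce. With 41 per group, the standardised difference detectable at 80% power is 0.626, which is 0.626 × 0.71 = 0.44 ng/mL, or 13% of 3.40 rather than 10%.

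**4. Power by evaluable number.** All rows use the two-sided t-test at 0.05. The third column takes the 80% at face value (standardised difference 0.626). The fourth uses the stated inputs (0.479). The last is the difference detectable with 80% power at SD 0.71. Every lost patient is counted as contributing nothing.

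| Evaluable per group | Loss from 44 | Power if 41 gave 80% | Power on stated inputs | Detectable difference |
|---|---|---|---|---|
| 41 | 7% | 80% | 57% | 0.44 ng/mL (13%) |
| 39 | 11% | 78% | 55% | 0.46 ng/mL (13%) |
| 37 | 16% | 76% | 53% | 0.47 ng/mL (14%) |
| 35 | 20% | 73% | 51% | 0.48 ng/mL (14%) |
| 30 | 32% | 66% | 45% | 0.52 ng/mL (15%) |

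On either basis, going from 41 to 35 costs 6 to 7 points of power, and going to 30 costs 12 to 14. The gap between the two power columns at 41 per group, 23 points, is larger than either.

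**The case against.** The strongest reply is that nothing in the documents shows the loss will exceed 5%. Entry is restricted to patients aged 18 to 65 who are hemodynamically stable and already on enteral feeding for at least 24 h (section 2.4). Sepsis, cirrhosis and acute renal failure are excluded (section 2.5). That may well lower early deaths and early exits. Two of the section 2.6 reasons, a short expected ICU stay and a contraindication to enteral nutrition, read more like screening conditions than losses after randomisation. This stands. A reader might infer that the 41 certainly will not be reached, but without any loss rate in the documents that is a prediction they do not support.

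A second reply concerns what counts as lost. Section 2.10.8 ends feeding at ICU discharge, but no section says that blood sampling ends there. Section 2.6 does not say whether its discharge rule means the ICU or the hospital. A patient who dies or leaves after day 5 can already have a day-5 value, and section 2.10.16 names longitudinal models that could use it. This also stands. It would be wrong to treat every ICU exit before day 10 as a complete loss, and the power rows above are pessimistic to that extent.

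A third reply is that the overstated power comes mainly from the base calculation and would be there with no attrition at all. That is correct, but it does not rescue the 5%. If only the base were corrected, the same unsupported allowance would be carried into the new number.

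**Conclusion.** The point holds in conditional form. The 5% is unsourced, gives a margin of 3 patients per arm, and is not reconciled with section 2.6 or with day-10 samples missing after death and possibly after ICU discharge. More than 3 losses in an arm puts it below 41. With independent losses, both arms keep 41 with probability 68% at 5% loss, 12% at 10% and under 1% at 15%.

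The effect on power is modest at moderate loss: about 2 points at 39 per group, 6 to 7 at 35 and 12 to 14 at 30, with less where day-5 values are used. The mismatch between the 41 and its stated inputs (69 to 70 needed, about 57% power at 41) is a separate and larger error. The two should be corrected together.

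**What to change.** In section 2.9:

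- Replace the 5% with an expected loss that covers the section 2.6 removals and missing post-baseline zonulin. Take it from the ICU's own recent records of patients who would meet sections 2.4 and 2.5.
- For the fixed 88 patients, restate the expected evaluable number per group, the power and the detectable difference over a range such as 10% to 30% loss. Use the stated 0.34 ng/mL and SD 0.71, and correct the base calculation in the same revision.

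In section 2.10.16, name the longitudinal model already listed there as the primary analysis. Include every randomised patient with a day-0 and at least one later zonulin value, so that day-5 results count when day 10 is missing. Section 2.6 must then be reconciled with that set, because as written it removes some of these patients.

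The trial registration section says recruitment has not started, so the cost is a revision of the text and a look at existing records. No extra patients are required. The price is a less favourable stated power.
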